### 11.3 Statistical criteria of termination of trial

As this is an explorative study there are no statistical criteria that would lead to termination of the trial. In terms of quantitative analysis, the results will be reported in any case, irrespective of the achieved sample size at the end of the trial duration.

## **11.4 Planned Analyses**

Baseline imbalance between groups will be tested with a student t-test. Differences in means between healthy participants and patients with CNLBP will be analysed with independent student t-tests. A mixed (2) Group x (2) ME ANOVA with repeated measures during ME will be conducted for each dependent variable individually (Pain VAS, Functional Status ODI, Postural Control COM and CM, Proprioception JRE, and Motor Equivalence UCM).

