| Inclusion / Exclusion criteria: | 
Inclusion criteria:
 
 
• Patients with clinically confirmed musculoskeletal low back pain (non-specific low back pain)
 
• VAS pain > 0; ODI>0
 
• Age ≥ 18 years
 
 
Exclusion criteria:
 
 
• Known or suspected neurological diseases or lesions
 
• Traumatic injury of musculoskeletal system (fractures, tumours)
 
• Spinal pathologies (e.g., tumour, infection, fracture, and inflammatory disease)
 
• Previous spinal surgery
 
• Presence of any contraindication to exercise (fracture or cardiovascular limitations)
 
• Pain in the neck or cervical spine that reduces active movement to less than 30° rotation to each side
 
• Whiplash during the last year
 
• Known vestibular pathologies
 
 
Healthy group:
 
Participants of the healthy group must be free of neurological or orthopaedic limitations to daily activity (VAS=0; ODI=0).
                                                                                                                                                                                                                      |

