| Number of Participants with Rationale: | 20 to 30 patients with low back pain (min. 10 per arm) and 20 healthy controls for the normative data. Based on previous studies with similar endpoints, the selected amount of participants has shown to suffice for an explorative approach with a desired power of 80% and an alpha of 0.05. |
| Study Duration:                        | September 2014 to December 2015                                                                                                                                                                                                                                                                 |
| Study Schedule:                        | Begin recruiting: January 2015
Last assessment: December 2015                                                                                                                                                                                                                                |
| Investigator and project leader:       | [name]
[contact]
[contact]                                                                                                                                                                                   |
| Study Centre:                          | Reha Rheinfelden
[name]

[name]                                                                                                                                                                                                                                   |
| Statistical Considerations:            | Student T-Test will be applied for group comparison at Baseline for cross-sectional comparison of LBP group with healthy group.

Repeated measure ANOVA with post-hoc analysis will be applied to test therapy effects.

Effect size will be calculated with Guyatt's effect size.  |
| GCP Statement:                         | This study will be conducted in compliance with the protocol, the current version of the Declaration of Helsinki, the ICH-GCP or ISO EN 14155 (as far as applicable) as well as all national legal and regulatory requirements.                                                                 |

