## 6. STUDY DESIGN

### 6.1 General study design and justification of design

The intended procedures and study stages are summarised in Table 1 and Figure 1. Patients will be recruited from the out-patient department of the study site (Reha Rheinfelden) and public advertisement. In a cross-sectional study, baseline (BL) values are recorded to assess and to identify expected discrepancies in postural behaviour in a group-wise comparison (healthy vs. patients with LBP). In a pilot randomised sham-controlled trial (RCT) with parallel groups and blinded assessors, the effects of added SMT to conventional therapy in comparison to added LIT will be evaluated on three additional measurement events. The primary endpoints are pain and function before ( $T_0$ ) and after 9 treatments during 5 weeks (twice a week). Short-term effects will be evaluated within a week after the last training session ( $T_1$ ). Long-term effects will be tested four weeks after the last training session ( $T_2$ ).

*Screening and pre-intervention assessments:* Potential participants will be informed (personal or by phone and email) of the study procedures, risks and expenses, and possible benefits (according to the patient information sheet approved by the competent ethical committee, CEC). After written and oral information, the patient will have one to three days to consider participation before giving informed consent. Once written consent is provided, a baseline measurement will take place 2 to 4 days prior to therapy commencement. For healthy participants there is no time constraint. An internal rheumatologist will confirm the diagnosis for patients who are not referred to the clinic by their treating physicians. The BL assessment will reveal whether all eligibility criteria are fulfilled and whether trial participation is granted. Patients will also be asked to give a second oral consent to further participate in the trial. Once included and randomised for treatment groups, all analysis will follow intention-to-treat principles (as-per-case analysis will also be conducted).  $T_0$  will be conducted immediately before first treatment to ensure a stable baseline (4 to 7 days after BL).

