**Figure 1: Study procedure flow-chart**

## 7. STUDY POPULATION

### 7.1 Eligibility criteria

Participants fulfilling all of the following inclusion criteria are eligible for the study:

- Patients with musculoskeletal low back pain (lumbosacral pain, with or without radicular pain).
- Pain and discomfort localized below the costal margin and above the inferior gluteal folds, with or without referred leg pain of at least 3 months' duration.
- Currently seeking care for low back pain.
- Age above 18 years.
- Comprehend German.
- Informed Consent as documented by signature (Appendix Informed Consent Form).

The presence of any one of the following exclusion criteria will lead to exclusion of the participant:

- Clinical signs of neurological damage (i.e. paresis or tingling in limbs).
- Traumatic injury to the musculoskeletal system, such as fractures or tumours.
- Suspected or confirmed spinal pathology (e.g., tumour, infection, fracture, and inflammatory disease).
- Previous spinal surgery.
- Major surgery scheduled during treatment or follow.
- Pain in the neck or cervical spine that reduces active movement to less than 30° rotation to each side
- Whiplash during the last year
- Known vestibular pathologies
- Inability to follow the procedures of the study, e.g. due to language problems, psychological disorders, dementia, etc. of the participant.
- Parallel participation in another study.
- Previous enrolment into the current study.
- Enrolment of the investigator, his/her family members, employees and other dependent persons.

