### 7.2 Recruitment and screening

The therapy management office will notify the PL when patients matching the inclusion criteria are referred to the outpatient department of the study site. The time lapse between referral and first treatment appointment is approximately 2 weeks. During this time the PL will contact the patient to inform about the study and invite him or her for a baseline assessment. Additionally, local care providers and physicians will be contacted and information leaflets provided to the public (online media, print media, local health institutes and Spa-Centres). These flyers will not be distributed before ethical approval for their content is given. Interested participants will contact the PL to receive detailed information (as described above). If the patient was not referred to study site by an external physician, they must first be examined by the clinic's internal rheumatologist to confirm diagnosis of chronic lumbosacral spinal pain (including radicular pain).

Healthy participants will be invited through homepage advertisement, local media, and internal pin-board (for staff members).

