### 9.2.3 Assessment of other outcomes of interest

At BL socio-demographic data will be recorded to characterise the included patients (age, gender, activity level, and profession).

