### **11.4.3 Secondary Analyses**

No secondary analysis is planned.

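### The patient-versus-healthy comparison is non-randomised and unmatched but analysed with an unadjusted t-test, so age, sex and activity can be confounded with low back pain status

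*Protocol*

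**What the plan says.** **Analysis.** Protocol 11.4 fixes the test: "Differences in means between healthy participants and patients with CNLBP will be analysed with independent student t-tests". The synopsis (Statistical Considerations) agrees: "Student T-Test will be applied for group comparison at Baseline for cross-sectional comparison of LBP group with healthy group". Neither names a covariate, a stratum or a matching factor. Section 11.4.1 intends no sub-group analysis, and 11.4.3 states "No secondary analysis is planned", so nothing elsewhere in the protocol adjusts this comparison.

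**Where the groups come from.** For patients, 6.1 says: "Patients will be recruited from the out-patient department of the study site (Reha Rheinfelden) and public advertisement". For the healthy group, 7.2 says: "Healthy participants will be invited through homepage advertisement, local media, and internal pin-board (for staff members". The only selection rule written for the healthy group is in the synopsis: "Participants of the healthy group must be free of neurological or orthopaedic limitations to daily activity (VAS=0; ODI=0". It concerns symptoms and limitations; it sets no age range, sex balance or activity level.

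**Covariates.** Section 9.2.3 says: "At BL socio-demographic data will be recorded to characterise the included patients (age, gender, activity level, and profession". The stated purpose is description, and of the patients.

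**Use of the comparison.** It is one of the two main objectives in the synopsis, the second of the three research questions in section 4, and the subject of hypotheses 2 and 3 in 11.1. The limitations in 6.1 do not discuss whether the two groups are comparable.

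**The concern.** Randomisation balances the two treatment arms against each other. It does nothing for patients against healthy volunteers. If the healthy group turns out younger, differently composed by sex, or more active, and if postural control or head repositioning varies with those factors, the raw difference in means mixes that variation with whatever belongs to low back pain. The t-test cannot separate the two, and a larger sample does not help, because the bias stays while the standard error shrinks.

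At stake is the reading of the cross-sectional result. Section 4.1 wants to evaluate the relationship between low back pain, postural control and cervical proprioception, and the synopsis calls the healthy data normative. An unadjusted difference supports neither use if the groups differ in age or sex.

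**Working it through.** **1. The plan's own figure.** The only power figure offered for the secondary hypothesis is in 11.2: power above 0.9, from a cited experiment with N = 9, mean difference 0.055 and SD 0.015. Treated as a paired t-test (two-sided 5%), d = 0.055/0.015 = 3.67 and power exceeds 0.999. Using the F of 25.8 quoted there instead, d = √(25.8/9) = 1.69 and power is 0.993. The figure reproduces. However, it concerns a within-subject contrast in healthy people; no figure in the protocol covers patients against healthy participants.

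**2. Inputs for the check.**
- Group sizes: 20 patients and 10 healthy (11.2), or 20 to 30 patients and 20 healthy (synopsis). The two places differ, so 20 v 10, 20 v 20 and 30 v 20 are all shown.
- Alpha 5% (11.2). Sidedness is not stated; two-sided is assumed.
- Assumed, not in the documents: one covariate differs between the groups by g = 0.5 to 1.0 SD and has within-group correlation r = 0.3 to 0.5 with the outcome. There is no true effect of low back pain.

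**3. Formula.** The bias in SD units is b = r × g, from 0.3 × 0.5 = 0.15 to 0.5 × 1.0 = 0.50. The t statistic is then noncentral with n₁ + n₂ − 2 degrees of freedom and noncentrality b/√(1/n₁ + 1/n₂). For 20 v 20 and b = 0.50: √(1/20 + 1/20) = 0.316, noncentrality 0.50/0.316 = 1.58, critical value 2.024 on 38 degrees of freedom, rejection rate 33.8%.

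**4. Rejection rate of the nominal 5% t-test with no true effect.**

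| g, r | Bias b (SD) | 20 v 10 | 20 v 20 | 30 v 20 |
|---|---|---|---|---|
| 0.5, 0.3 | 0.15 | 6.6% | 7.5% | 8.0% |
| 0.5, 0.5 | 0.25 | 9.6% | 12.0% | 13.6% |
| 1.0, 0.3 | 0.30 | 11.6% | 15.2% | 17.5% |
| 1.0, 0.5 | 0.50 | 23.9% | 33.8% | 39.7% |

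In every row the rate rises with sample size.

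**5. The same settings with the covariate in the model.** A simulation with 8,000 runs per setting gives 4.5% to 5.3% for 20 v 10 and 4.8% to 5.3% for 20 v 20. The simulation error is about √(0.05 × 0.95/8000) = 0.24 percentage points, so these agree with 5%. The simulation used one covariate, measured without error and linearly related to the outcome; 30 v 20 was not simulated.

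**6. Scale.** The difference detectable with 80% power (two-sided t-test) is 1.12 SD at 20 v 10, 0.91 SD at 20 v 20 and 0.83 SD at 30 v 20. A bias of 0.50 SD is therefore 0.50/1.12 = 45% to 0.50/0.83 = 60% of the effect that the comparison could reliably find.

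**The case against.** Several objections have force.

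- **No imbalance is shown.** A reader might infer that the healthy group is in fact younger or fitter, or that it contains clinic staff. The documents do not say so. Staff are invited by pin-board, and no group difference in any covariate is reported. Patients are also recruited by public advertisement, so the recruitment routes overlap. What stands is that such differences are possible and uncontrolled.
- **The study is explorative, and hypotheses 2 and 3 speak of group differences, not causes.** This limits the weight of the point. It does not remove it, because section 4.1 asks about the relationship with low back pain.
- **The comparison does not decide whether the training is justified.** A reader might infer that a spurious deficit would validate the intervention. The rationale in section 3 rests on prior literature and belief, patients go from baseline to treatment within days, and efficacy is tested in the randomised arms. That inference is not supported.
- **The staff pin-board seems to contradict 7.1.** The exclusion list there includes "Enrolment of the investigator, his/her family members, employees and other dependent persons". However, the inclusion criteria in the same section require low back pain of at least three months and current care-seeking, which healthy participants cannot meet, so the list may apply to patients only. This is an ambiguity, not an established contradiction.
- **The covariates may be collected in controls.** Table 1 places socio-demographic data at the baseline visit, which healthy participants attend, and 9.2.1 has the subject complete a personal data sheet. Section 9.2.3 mentions patients only. This needs clarifying, and recording alone does not adjust the analysis.
- **A statistical analysis plan could add covariates.** None is at hand, and the protocol itself names the unadjusted test twice.

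The test of baseline imbalance in 11.4 does not answer the point: it does not name the healthy group, and a test adjusts nothing.

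**Conclusion.** The point holds as a weakness of the planned analysis for hypotheses 2 and 3: the protocol fixes an unadjusted t-test for a non-randomised, unmatched comparison and leaves age, sex and activity uncontrolled. The documents do not show that confounding is present. The range of 6.6% to 39.7% against a nominal 5% depends on the assumed covariate gap and correlation. Its upper end needs a full 1 SD gap with correlation 0.5; at the mild end (0.15 SD) the excess over 5% is only 1.6 to 3.0 percentage points. The change is worth making because it is cheap and the comparison is a stated main objective. The randomised comparison of pain and function is untouched.

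**What to change.** **Required.**
- In 11.4 and in the synopsis (Statistical Considerations), replace the t-test for patients against healthy participants by a linear model for each baseline outcome with group, age and sex. Report the adjusted mean difference with its 95% confidence interval.
- Add activity level as a sensitivity analysis only, since pain may itself reduce activity and full adjustment could remove part of the association of interest.
- In 9.2.3, state that age, gender, activity level and profession are recorded in healthy participants as well as patients.
- Clarify whether the employee exclusion in 7.1 applies to healthy participants, given the staff pin-board in 7.2.

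**Cost.** A change of wording and two degrees of freedom: 28 to 26 at 20 v 10, 38 to 36 at 20 v 20, 48 to 46 at 30 v 20. If the groups do differ, precision also changes somewhat. For one covariate at 20 v 20 with g = 1, the variance is multiplied by about (1 + 0.25 × 1²)(1 − r²), which is 1.25 × 0.91 = 1.14 for r = 0.3 and 1.25 × 0.75 = 0.94 for r = 0.5. The standard error therefore changes by about +7% or −3%.

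**Optional.** Matching healthy participants to patients by age and sex is possible but not needed for this fix. Recruiting controls after the patients would have to fit a last assessment in December 2015, would tie group to calendar time, and would leave very few people per cell if there are only 10 controls.

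Adjustment deals only with the covariates in the model; the adjusted difference remains an association.

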## 11. STATISTICAL METHODS

### 11.1 Hypothesis

- |                            |                                                                                                                                                                                                                      |
|----------------------------|----------------------------------------------------------------------------------------------------------------------------------------------------------------------------------------------------------------------|
| 1° Null Hypothesis:        | Functional status and self-reported pain will reduce significantly in both groups, CG and EG, but no group interaction is expected.                                                                                  |
| 1° Alternative Hypothesis: | EG will show significantly more improvement in all primary and secondary outcomes as compared to CG.                                                                                                                 |
| 2° Null Hypothesis:        | Compared to healthy controls, patients with CNLBP will show no difference in postural control with optimal joint configuration variability when adjusting COM after destabilisation as compared to healthy controls. |
| 2° Alternative Hypothesis: | Patients with CNLBP will show different postural variability to adjust to destabilisation as compared to healthy controls.                                                                                           |
| 3° Null Hypothesis:        | Compared to healthy controls, patients with CNLBP will show no difference in cervical proprioception acuity as compared to healthy controls.                                                                         |
| 3° Alternative Hypothesis: | Patients with CNLBP will show reduced cervical proprioception acuity as compared to healthy controls.                                                                                                                |

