### 11.2 Determination of Sample Size

This is the first study of its kind to investigate the effects of a sensorimotor training on dynamic postural control in patients with CNLBP and is therefore of explorative nature. Related to the primary hypothesis, however, a study using the same outcomes investigated the effects of treadmill training on gait in down-syndrome children and compared them to healthy subjects [29]. Although this is not a comparable study population it was used to estimate the power of the test. With a mean between-group difference of 1.4 and a pooled standard deviation of 0.19 the study revealed highly significant group effects ( $N=15$ ,  $p<0.01$ ).

Several studies have investigated the effects of sensorimotor training on pain and functional status. Two of the most recent ones [30, 31] have found significant time and group interactions using the same outcomes. Applying the results of these studies to a sample size calculation with an alpha value of 5% and the desired power 80%, it is expected that 10 patients per arm would suffice to reveal group differences and to detect change.

In terms of the secondary hypothesis, it must be referred to an article which used a similar motor task in an experimental setup with cross-sectional analysis of healthy participants. For the detection of within-subject difference of control parameters of the uncontrolled manifold approach, Scholz et al. [27] found that with a deflection of 0.06 m, the projections of joint configurations to the manifold differed significantly to the projection in the range space ( $N=9$ ,  $F_{1,8}=25.8$ ,  $p<0.001$ ). With a mean difference of 0.055 and a standard deviation of 0.015, this calculates to a power of  $>0.9$ .

Considering these findings and taking into account the explorative approach of this trial, a total number of 30 participants is planned (10 healthy subjects and 10 patients per intervention arm).

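### Patients and healthy controls are compared by the Student t-test at mostly unequal planned sizes, so its 5% level and power are not assured if the two spreads differ; Welch's test should be named

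*Protocol*

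**What the plan says.** Section 11.4 fixes the test for patients against healthy controls: "Differences in means between healthy participants and patients with CNLBP will be analysed with independent student t-tests". The synopsis repeats it for the baseline data: "Student T-Test will be applied for group comparison at Baseline for cross-sectional comparison of LBP group with healthy group". Neither place mentions an unequal-variance form, and section 11.4.6 says that no departures from the plan are intended.

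The group sizes appear twice and differ. Section 11.2 gives "10 healthy subjects and 10 patients per intervention arm", which is 20 patients against 10 healthy people once the two arms are combined. The synopsis gives "20 to 30 patients with low back pain (min. 10 per arm) and 20 healthy controls for the normative data".

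The comparison decides hypotheses 2 (postural control) and 3 (cervical proprioception) in section 11.1. The synopsis states an alpha of 0.05 and a power of 80% for the planned numbers. Section 11.2 gives one SD for the secondary hypothesis. It is a within-subject figure from nine healthy people and says nothing about the spread between patients or between controls.

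**The concern.** The pooled test estimates one common variance, weighted towards the larger group. When sizes and variances both differ, the standard error is systematically wrong, even if the groups are perfectly matched on age, sex and everything else.

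The direction depends on which group is more variable. If it is the larger group (patients), the test is too strict and loses power in an already small sample. If it is the smaller group (healthy), it declares too many differences. The protocol documents neither case and excludes neither.

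The size ratio is not protected either. Patients are measured at baseline before deciding whether to enter the randomised part (synopsis, Measurements and procedures), so the cross-sectional set can hold more patients than are randomised. Section 11.3 reports results whatever sample size is reached.

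**Working it through.** **Inputs from the protocol.** Alpha 0.05. Sizes 20 versus 10 (section 11.2), and 20 versus 20 up to 30 versus 20 (synopsis).

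**Assumptions.** Two-sided test (sidedness is not stated); normal outcomes; Student read as pooled-variance; ratio of SDs 1.5 or 2 in either direction (the protocol gives none).

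**Step 1: the error in the standard error.** With patients n1, s1 and healthy n2, s2:

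- expected pooled variance of the mean difference: [(n1−1)s1² + (n2−1)s2²]/(n1+n2−2) × (1/n1 + 1/n2)
- true variance: s1²/n1 + s2²/n2

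At 20 versus 10, patient SD double (s1=2, s2=1): (19×4 + 9×1)/28 × 0.15 = 0.455, against 4/20 + 1/10 = 0.300. The ratio is 1.52, so the standard error is about 23% too large.

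At 20 versus 10, healthy SD double (s1=1, s2=2): (19×1 + 9×4)/28 × 0.15 = 0.295, against 1/20 + 4/10 = 0.450. The ratio is 0.65, so the standard error is about 19% too small.

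At 20 versus 20, either SD double: (19×4 + 19×1)/38 × 0.10 = 0.25, against 4/20 + 1/20 = 0.25. The ratio is exactly 1.

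**Step 2: true error at nominal 5%.** Simulated with 2,000,000 runs per case. Equal SDs return the planned 5.0% for the pooled test at all three sizes.

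| Patients vs healthy | Patient SD 1.5× / 2× healthy | Healthy SD 1.5× / 2× patient |
|---|---|---|
| 20 vs 10 | 2.7% / 1.9% | 8.6% / 11.3% |
| 30 vs 20 | 3.5% / 2.9% | 7.0% / 8.5% |
| 20 vs 20 | 5.1% / 5.2% | 5.1% / 5.2% |

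Welch's test stays between 4.9% and 5.1% in all of these cases.

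**Step 3: power.** The true difference is set at 2.9 true standard errors, where Welch's test has about 80% power when patients are as variable as controls or more so.

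| Patients vs healthy | SD ratio (patient/healthy) | Student | Welch |
|---|---|---|---|
| 20 vs 10 | 1 | 80% | 78% |
| 20 vs 10 | 1.5 | 71% | 79% |
| 20 vs 10 | 2 | 65% | 80% |
| 30 vs 20 | 1 | 81% | 81% |
| 30 vs 20 | 2 | 73% | 81% |

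The equal-SD rows give the price of using Welch's test when it is not needed: about 2 points at 20 versus 10 and almost nothing at 30 versus 20. At 30 versus 10, a mix of the two places that neither one plans, it is about 3 points (80.6% against 77.3%).

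**The case against.** The strongest reply is that nothing in the protocol shows unequal variances on the tested outcomes, and most of it stands.

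- A reader might infer that the groups are selected to differ in spread, since healthy participants must have VAS=0 and ODI=0 while patients need only exceed zero. That holds for pain and disability alone. Hypotheses 2 and 3 concern postural control and head repositioning, on which the protocol sets no range. Patients are themselves narrowed by excluding vestibular pathology, recent whiplash and severely restricted neck rotation.
- A reader might take hypothesis 2 as an admission of unequal variances: "Patients with CNLBP will show different postural variability to adjust to destabilisation as compared to healthy controls". It is not. The variability meant there is joint-configuration variability during the task, which is the outcome whose mean is compared. A difference in that mean says nothing about SDs between people.
- A reader might conclude that the 5% level is broken. If patients are the more variable group, false positives stay below 5% and the loss is power. Inflation requires healthy people to be more variable, and no section suggests that.
- The synopsis allows 20 versus 20, where the issue disappears.
- The protocol never says pooled, and an analysis plan not at hand could specify the form.

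On the last point, the protocol does not leave the test open: it names Student's test twice. If Welch's form was meant, one word settles it. What survives the other points is narrower: equal variances are unsupported, most of the planned sizes are unequal, and the named test depends on one or the other being equal.

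**Conclusion.** The point holds conditionally. With unequal sizes the Student test holds its nominal level only if the two SDs are equal, and the protocol gives no basis for assuming that they are. The possible departures are material at 20 versus 10, moderate at 30 versus 20 and negligible at 20 versus 20. Their direction is unknown.

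The figures rest on assumed SD ratios of 1.5 to 2, normality and two-sided testing. They show what could happen and do not predict what will.

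The comparison is secondary and the study calls itself explorative, so this is a minor improvement and not a flaw that threatens the trial. The disagreement between 10 and 20 healthy controls is a separate matter that needs reconciling. Settling it at 20 would not remove this point if more than 20 patients are measured.

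**What to change.** In section 11.4 and in the synopsis (Statistical Considerations), name Welch's unequal-variance t-test for the comparison of patients with healthy controls, and report the mean difference with its Welch 95% confidence interval.

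This changes one phrase in two places and one software option, with no effect on data collection. The only statistical price is the small loss of power under equal variances shown in the power table.
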